## Abstract

**Background:**

Binge eating disorder is characterized by recurrent episodes of binge eating accompanied by a sense of lack of control. Of the different treatments available, Cognitive Behavioral Therapy-Enhanced and guided self-help treatment are recommended. As online treatment offers several additional advantages, we have developed a CBT-Enhanced online guided self-help intervention. The aim of this study is to determine whether this intervention reduces eating disorder pathology and increases the amount of binge free days in adults classified with binge eating disorder or other specified feeding or eating disorder- binge eating disorder, compared to an untreated waiting list condition. The experimental condition is hypothesized to be superior to the waiting list condition.

**Methods:**

The efficacy of an online guided self-help intervention for binge eating disorder will be assessed by conducting a randomized controlled trial. The trial will target adult individuals classified with binge eating disorder or other specified feeding or eating disorder- binge eating disorder with a body mass index between 19.5 and 40, referred to an eating disorder treatment center. Dual arm allotment will be performed in a 1:1 ratio stratified for BMI above or below 30. Randomization will be blinded to the online intervention (*n* = 90), or to the control waiting list condition (*n* = 90). Assessors will be blinded and assessments will be administered at baseline, week 5, at end-of-treatment, and at 12 and 24 weeks follow-up. Primary outcome will be eating disorder pathology, operationalized as number of days on which binge eating occurred between the two conditions during the period of the intervention. Secondary outcome measures will be differences in other eating disorder pathology, clinical impairment and in quality of life, while therapeutic alliance, demographic characteristics and followed treatment module will serve as effect moderators. Several types of costs will be assessed.

**Discussion:**

This paper presents an online guided self-help Cognitive Behavioral Therapy- Enhanced study protocol for individuals classified with binge eating disorder or other specified feeding or eating disorder. Efficacy will be examined through a Randomized Controlled Trial.

**Trial registration:**

The study protocol is registered with the Netherlands Trial Registry NTR (NTR 7994) since 6 September 2019.

## Background

Eating disorders, one of the three most common disorders in adolescents [1], have a life time prevalence in the Netherlands of 1.74% [2]. These disorders, which have a significant impact on the psychological and physical well-being of affected individuals [3], are characterized by over-evaluation of shape and weight [4]. Binge eating disorder (BED) is specifically characterized by recurrent episodes of binge eating accompanied by a sense of lack of control [5]. The binges occur at least once a week and, if they are less frequent, the individual is classified with other specified feeding or eating disorder (OSFED) BED [5]. Of the population in the West, 2% suffers from binge eating disorder [6], and 1.5% from OSFED [7].

Of the range of treatments available for eating disorders, including Cognitive Behavioral Therapy (CBT), Dialectical Behavioral Therapy (DBT) and Interpersonal Therapy (IPT), Cognitive Behavioral Therapy-Enhanced (CBT-Enhanced) [8–10] is the preferred evidence based treatment for BED [9]. According to Fairburn, developer of CBT-Enhanced, [11, 12], CBT-Enhanced treatment leads to a recovery rate of 50–65% amongst the individuals with an eating disorder. For BED specifically, the recovery rate is 54% [12]. However, as, according to the stepped care principle, CBT-Enhanced could be too intensive for individuals suffering from BED or OSFED BED, international guidelines have recently recommended guided self-help treatment as first step for individuals suffering from BED [9]. Most online interventions are based on existing face to face treatment protocols [13]. Guided self-help has the advantages of reduced travel costs and travel time for the patient [14], less time of a specialist’s invested in a single treatment [15], and the removal of geographical distance as a barrier to seeking treatment [16]. In addition, an online guided self-help version of CBT-Enhanced (GSH CBT-E) follows all recommended evidence-based guidelines for individuals suffering from BED [9].

Studies have shown that several online self-help treatments, including the use of apps on different devices such as smartphones or computers, are effective when combined with therapeutic support [17]. This is also the case for BED [17, 18], and a recent meta-analysis showed that 46% of the individuals classified with BED report not to suffer from binge eating episodes after self-help treatment [19]. There are, however, differences in the efficacy of self-help treatment [18], with guided self-help (GSH) being found to be more effective than non-guided self-help [20], and a stronger therapeutic alliance improving treatment efficacy [21, 22]. The literature further suggests therapeutic alliance to be stronger when contact is synchronous as by phone than when asynchronous as by email [21].

Responding to the absence of CBT-Enhanced based guided self- help (GSH) in Dutch, Novarum, Center for Eating Disorders in the Netherlands, has developed a CBT-Enhanced based GSH (GSH CBT-E), based on the self-help section (Part two) of *Overcoming Binge Eating, The Proven Program to Learn Why You Binge and How You Can Stop* [23]. A study of GSH for BED by Ter Huurne et al., based on general Cognitive Behavioral Therapy (CBT) and Motivational Interviewing (MI), in the Netherlands have shown that, compared to a waiting list condition, an online GSH version of Cognitive Behavioral Therapy (GSH CBT), is particularly effective in reducing eating disorder pathology. At the same time, reduction in binge eating episodes, the main symptom in individuals suffering from BED, has not been reported [24]. Although one GSH CBT study in Germany did show a reduction of binge eating episodes of 58% [25], the treatment protocols used in both studies, in the Netherlands as well as in Germany, were not based on CBT-Enhanced, and a GSH version of CBT-Enhanced is expected to be more effective than GSH CBT [21, 26].

To broaden the treatment method to CBT-Enhanced, in this study, contact with the participants in this study will be synchronous, using direct phone contact, unlike in Ter Huurne et al. [24], where patient contact was asynchronous, through email [21, 22, 24]. Again extending Ter Huurne et al. [24], which was conducted with only female participants [24], this study will include both male as well as female participants. Thus, even though gender is not expected to influence treatment efficacy [27], the results will be relevant to both genders. Finally, where Ter Huurne et al. [24] used self-report questionnaires to classify study participants and assess eating disorder pathology, including pre- and post-treatment binge eating behavior, this study will use the Eating Disorder Examination (EDE) interview [28] as well as self-report questionnaires [29].

The primary aim of this study is to examine the efficacy of online GSH CBT-E with regard to eating disorder pathology, operationalized as difference in the number of binge-free days among men and women classified with BED and/ or OSFED BED after treatment compared to a waiting list control group. The secondary aim is to examine the efficacy with regard to other eating disorder pathology, clinical impairment and quality of life between GSH CBT-E and a waiting list control group after treatment and during the follow-up period. Tertiary aim is to calculate direct treatment costs for the GSH CBT-E intervention for means of transparency, direct comparison with the waiting list condition, and indirect comparisons with other interventions. Efficacy will be examined through a parallel group randomized controlled trial.

It is hypothesized that GSH CBT-E is superior to the waiting list condition with regard to a decrease in eating disorder pathology and clinical impairment. GSH CBT-E is also expected to be superior to the waiting list with regard to increase in the number of binge free days and quality of life.

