**Fig. 1 Fig1:**
[figure not shown]
Flow chart of planned intervention and assessment

Participants are referred for treatment by general practitioners, secondary care health professionals or general hospitals. All potential participants are over 18 years of age and are being treated voluntarily. All potential participants classified with BED or OSFED BED, assessed by a clinical psychologist or psychiatrist, are invited to participate in the study. If a potential participant meets all inclusion and none of the exclusion criteria, agrees to the terms and conditions of the study and has provided informed consent, a baseline assessment (T0) will be scheduled. After the baseline assessment is completed, participants will be randomized to either the experimental condition (GSH CBT-E) or the waiting list control condition. Randomization will be blinded and stratified for body mass index (BMI) above or below 30. BMI will be calculated as weight in kg/ height in m^2^. Participants assigned to the experimental condition will start their treatment directly after they read the mandatory literature. The control group will start treatment after a waiting list period of 12 weeks, the same duration as the intervention. After baseline (T0), assessments will take place four times during and after treatment: at week 5, which is the evaluation-point of treatment for GSH CBT-E (T1); at the end of treatment for GSH CBT-E/ start of treatment for waiting list control group (week 12, T2); at 12 weeks after treatment for GSH CBT-E/ End of treatment for the waiting list condition (week 24, T3); and at 24 weeks after treatment for GSH CBT-E/, 12 weeks after treatment for waiting list control group (week 36, T4). The initial screening, before consent to study participation will take place at Novarum, but the intervention and assessments will take place at any location where participants have internet connection and are able to focus on their sessions. Since a large proportion of the Dutch population (96.7%) had internet access in 2018 [33], the participants’ personal location can be anywhere in the Netherlands. Obtained close- out period will be 1.5 years.

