### Intervention and procedure

All participants will receive GSH CBT-E: the experimental group will receive treatment immediately after baseline assessment, and the control group after a 12 weeks waiting period. GSH CBT-E is an online guided self-help version of CBT-Enhanced [8], based on *Overcoming Binge Eating, The Proven Program to Learn Why You Binge and How You Can Stop* [23], whose second part, a self-help guide, has been transformed into an online intervention.

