##### Waiting list control group

Participants assigned to the non- experimental (waiting list) condition will start their GSH CBT-E treatment 12 weeks after baseline. This control condition will be a minimal intervention. Participants will be called every 6 weeks for a short conversation (10 min at most), which will include checking on the eating disorder symptoms and other important areas of the participant’s life. This is necessary as, under Dutch law, monitoring participants during their waiting list period is mandatory at least every 6 weeks.

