## Discussion

This paper presents a study protocol of an RCT on the efficacy of online GSH CBT-E treatment for individuals suffering from BED and/or OSFED BED. GSH CBT-E is the first treatment in the Netherlands to follow all NICE [9] guidelines for BED: according to these guidelines is CBT-Enhanced the preferred treatment and that treatment should be offered through the stepped care principle, and recommending guided self-help treatment. The primary goal of GSH CBT-E is to increase the amount of binge free days; secondary goals are to decrease eating disorder pathology and clinical impairment related to the eating disorder and to improve quality of life. Short term efficacy will be assessed directly post treatment, long-term effects will be assessed 12 and 24 weeks post treatment. Direct treatment costs of the intervention will also be calculated.

GSH CBT-E has several strengths. A guided self-help variation of CBT-Enhanced, it meets all recent guidelines for individuals suffering from BED. In addition, since participants can participate in their personal environment, GSH- CBT-E enables individuals to overcome barriers they may experience with face to face treatments, such as stigma, travel time and costs and availability [14–16]. GSH CBT-E will also reduce specialist’s time invested in a single treatment [15]. Based on the number of referrals, we expect to include 12 patients a month, which should be sufficient to result in a final sample size of 180 participants, allowing for a drop-out rate of 25% [19].

This study may also face some challenges. Participants and therapists might not feel comfortable working in an environment that is solely online and phone based due to a lack of face to face contact, or because they might face challenges navigating within the program. Therapists and participants might also experience issues with wireless connection, reception and malware. Therapists may also find it challenging to adapt to the role of guiding self-help therapy rather than providing face to face therapy. Although after the initial session, there is no face to face contact between assessors, therapists and participants, attention will be paid to adverse events, harms or differences in disease state.

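### The follow-up half of the secondary aim names a waiting-list comparison that the design cannot supply, because all controls start GSH CBT-E at week 12

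*Protocol article*

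**What the plan says.** The aims at the end of the Background section set the secondary comparison as efficacy on clinical impairment, quality of life and eating disorder pathology other than binge days, compared "between GSH CBT-E and a waiting list control group after treatment and during the follow-up period".

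Three other places describe what happens to that control group:

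- Trial design (text with Fig. 1): "The control group will start treatment after a waiting list period of 12 weeks, the same duration as the intervention". The same paragraph labels the week-24 assessment as "12 weeks after treatment for GSH CBT-E/ End of treatment for the waiting list condition (week 24, T3") and the week-36 assessment (T4) as 24 weeks after treatment for the experimental arm and 12 weeks after treatment for the control arm.
- Intervention and procedure: "All participants will receive GSH CBT-E", the experimental arm straight after baseline "and the control group after a 12 weeks waiting period".
- Waiting list control group: these participants "will start their GSH CBT-E treatment 12 weeks after baseline".

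The Statistical analysis section places the primary endpoint at 12 weeks after randomization. No section redefines what is compared at weeks 24 and 36.

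**The concern.** The aim names a comparator, a waiting list, for a period in which nobody is planned to be on one. A comparison of the randomized arms at weeks 24 and 36 is still possible, but it answers a different question: whether starting GSH CBT-E 12 weeks earlier leaves people better off later. The arms also stand at different distances from their own treatment at each of these visits.

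Interpretation is what is at stake. The Assessment section justifies follow-up by expecting the treatment effect to persist. If it does, and the controls respond in the same way once treated, the arms converge. A durable treatment would then show little or no difference at follow-up. Set against the aim as worded, that result could be taken as efficacy fading, when it would be what success looks like in this design.

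**Working it through.** **Step 1: planned exposure at each visit.** Inputs are the 12-week course, the start at week 0 or week 12, and the assessment weeks, all from Trial design. Weeks of GSH CBT-E completed by week w are min(12, w) in the experimental arm and max(0, min(12, w − 12)) in the control arm.

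| Visit | Experimental arm | Control arm | Weeks since end of treatment (experimental / control) |
|---|---|---|---|
| T1, week 5 | 5 | 0 | in treatment / untreated |
| T2, week 12 | 12 | 0 | 0 / untreated |
| T3, week 24 | 12 | 12 | 12 / 0 |
| T4, week 36 | 12 | 12 | 24 / 12 |

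Untreated control data exist only at weeks 5 and 12. At weeks 24 and 36 both arms have had the full planned course.

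**Step 2: reproduce the protocol's planning figure.** Sample size and power calculation gives d = 0.47, two-sided α = 0.05, 80% power and 72 per arm. By the normal formula, n = 2 × (1.96 + 0.84)² / 0.47² ≈ 71, and the working calculation rounds up to 72. The two-sample t-test gives 72.04 per arm, with power 0.7998 at 72. The stated figure is reproduced.

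**Step 3: illustrate the follow-up contrast.** Let f be the share of the effect that the delayed arm gains once treated. The protocol gives no value for f, so it is run from 0 to 1. Assume also that the immediate arm keeps its effect in full. The remaining difference is d × (1 − f), and power is for a two-sided t-test with 72 per arm.

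| Assumed f | Remaining d = 0.47 × (1 − f) | Power |
|---|---|---|
| 0% | 0.47 | about 80% |
| 25% | 0.35 | about 56% |
| 50% | 0.24 | about 29% |
| 75% | 0.12 | about 11% |
| 100% | 0 | 5% (the α level) |

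The value 0.47 is the protocol's assumption for binge eating. The aim in question covers other outcomes, so the table shows only the direction and possible range of the shrinkage. It is not a forecast for those outcomes.

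**The case against.** The strongest defence is that the phrase for the control group is simply the name of a randomized arm. Trial design uses it that way even at week 36, when that arm has been treated. On this reading the aim asks for a comparison of the two arms at T3 and T4, and that comparison exists. The delayed start is also fully disclosed, which makes a naive reading of a null result less likely.

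Part of this stands: the randomized contrast is real, and the timetable is open. It does not rescue the aim, which is stated as efficacy. A contrast between immediate and delayed treatment does not estimate efficacy against a waiting list, whatever the arms are called. Nor is this a detail to leave to an analysis plan, since no model can supply untreated controls at weeks 24 and 36.

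A reader might infer three stronger things that the document does not support:

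- *That the mixed model will dilute the treatment effect by averaging over all visits.* Statistical analysis says only that generalized linear mixed models will be used. It plans no such averaging, and the choice of time terms and contrasts is commonly left to an analysis plan.
- *That the Discussion repeats the error by saying that "long-term effects will be assessed 12 and 24 weeks post treatment".* That sentence names no comparator and fits within-arm maintenance equally well.
- *That the main result of the trial is compromised.* The primary endpoint falls at week 12, when the control arm is still untreated.

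**Conclusion.** The point holds for one part of one aim. The follow-up half of the secondary aim cannot be answered as written, because the stated design has no waiting-list condition after week 12. This follows from the protocol's own timetable and needs no numerical assumption.

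The size of the distortion cannot be fixed from the document. With the planning d = 0.47 as an illustration, assumed catch-up between 0 and 100%, and a fully maintained effect in the immediate arm, the follow-up difference lies between 0.47 and 0. It reaches zero only with full catch-up, so a zero difference is not the necessary expectation. But neither a small nor a null difference could be read as loss of efficacy.

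The primary endpoint, the week-12 part of the secondary aim and the sample-size calculation are untouched. This should be corrected, but it does not threaten the trial's main conclusion.

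**What to change.** Amend the secondary aim and the matching description of the analysis:

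1. Limit between-arm efficacy claims against the waiting list to T1 and T2, with week 12 as the main contrast for the secondary outcomes as well.
2. Restate follow-up as two separate objectives: (a) maintenance within the GSH CBT-E arm, labelled as uncontrolled; and (b) a randomized comparison of immediate with delayed start at T3 and T4, labelled as such, noting that the arms differ in time since treatment.
3. State in advance that a small or null difference under (b) is not evidence that the effect was lost.

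The cost is rewording one aim and the follow-up analysis. No new data, additional participants or changes to treatment are needed. The real price is a weaker long-term claim: the trial will not be able to report efficacy against no treatment beyond week 12. The change is best made before outcome data are examined, because a later one would look driven by the results.

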## Methods

### Trial design

A single center randomized controlled trial (RCT) will be conducted at Novarum, center for eating disorders in Amsterdam, the Netherlands. Participants in the experimental condition (GSH CBT-E) will be compared to the waiting list control condition. To our knowledge this is the first study examining efficacy of GSH CBT-E, since only efficacy results of GSH CBT have been reported [30–32]. Therefore, outcome of GSH CBT-E will first be compared to waiting list control condition. Figure 1 presents a flowchart of this study.

**Fig. 1 Fig1:**
[figure not shown]
Flow chart of planned intervention and assessment

Participants are referred for treatment by general practitioners, secondary care health professionals or general hospitals. All potential participants are over 18 years of age and are being treated voluntarily. All potential participants classified with BED or OSFED BED, assessed by a clinical psychologist or psychiatrist, are invited to participate in the study. If a potential participant meets all inclusion and none of the exclusion criteria, agrees to the terms and conditions of the study and has provided informed consent, a baseline assessment (T0) will be scheduled. After the baseline assessment is completed, participants will be randomized to either the experimental condition (GSH CBT-E) or the waiting list control condition. Randomization will be blinded and stratified for body mass index (BMI) above or below 30. BMI will be calculated as weight in kg/ height in m^2^. Participants assigned to the experimental condition will start their treatment directly after they read the mandatory literature. The control group will start treatment after a waiting list period of 12 weeks, the same duration as the intervention. After baseline (T0), assessments will take place four times during and after treatment: at week 5, which is the evaluation-point of treatment for GSH CBT-E (T1); at the end of treatment for GSH CBT-E/ start of treatment for waiting list control group (week 12, T2); at 12 weeks after treatment for GSH CBT-E/ End of treatment for the waiting list condition (week 24, T3); and at 24 weeks after treatment for GSH CBT-E/, 12 weeks after treatment for waiting list control group (week 36, T4). The initial screening, before consent to study participation will take place at Novarum, but the intervention and assessments will take place at any location where participants have internet connection and are able to focus on their sessions. Since a large proportion of the Dutch population (96.7%) had internet access in 2018 [33], the participants’ personal location can be anywhere in the Netherlands. Obtained close- out period will be 1.5 years.

